## Abstract

**Background:**

Over the past decade, many well-resourced health plans and systems surpassed the 80% colorectal cancer screening rate goal, while lower resource environments such as federally qualified health centers (FQHCs) lag behind. FQHCs in rural areas are especially challenged with limited resources to reach diverse patients who often lack consistent engagement with clinical care. mHealth solutions, like mPATH^®^CRC, can address these challenges by automating tasks and expanding patient outreach. This platform identifies patients due for CRC screening, educates them on the commonly used screening tests, and helps them select their best option. This paper describes protocols for a study that will implement mPATH^®^CRC in FQHCs using a novel outreach strategy that engages patients outside of regular appointments.

**Methods:**

Following a type 1 hybrid effectiveness-implementation design, we will conduct a patient-level randomized controlled trial (RCT) to assess the effectiveness of mPATH^®^-CRC over a three-year period. Embedded within the RCT, we will utilize a convergent, mixed methods design for evaluation of the implementation process. The planned trial sample will include 1000 patients who are at average CRC risk and due for screening. Participants will be randomized 1:1 to receive either usual care or outreach through mPATH^®^-CRC that includes text messages about screening, multi-media education on screening options, and either mailed FIT or assistance to schedule a colonoscopy. The primary outcome is completion of any CRC screening test within six months of randomization. We will also use surveys and interviews with FQHC personnel to explore integration of mPATH^®^-CRC into clinical workflows and sustainability challenges.

**Discussion:**

This trial will generate insights into the effectiveness and implementation of a digital CRC screening intervention in resource-limited FQHCs. Findings will inform strategies for optimizing outreach components and scaling implementation in similar settings.

**Trial registration:**

This trial was registered on June 4, 2024, at ClinicalTrials.gov (identifier NCT06441487).

**Supplementary Information:**

The online version contains supplementary material available at 10.1186/s12913-025-13262-y.

## Background

There are inequities in colorectal cancer (CRC) screening by intersecting characteristics of race, geography, and insurance status. Despite national declines in CRC incidence and mortality due to increased screening, significant disparities remain. Among adults aged 50–75, CRC screening rates are 69% for white individuals compared to 66% for Black, 59% for Hispanic, and 56% for American Indian individuals. Inequities are more pronounced in rural areas where screening rates are 5–6% lower than urban areas across racial groups [1–3]. Furthermore, only 54% of Medicaid and 30% of uninsured individuals are up-to-date with screening compared to 80% or more of those with private insurance or Medicare [4]. Higher screening rates are often driven by well-resourced health plans and systems that have the capacity and resources to implement evidence-based patient and provider outreach and education strategies [5]. Meanwhile, federally qualified health centers (FQHCs) have limited resources to reach patient populations with a disproportionate burden of healthcare needs. It is imperative that research focuses on approaches that reach and resonate with rural, racially diverse patients and the clinics that serve them.

Interventions that combine multiple evidence-based strategies that work in synergistic or complementary ways have been shown to improve CRC screening more than singular strategies [6, 7]. For example, decision aids, especially among low-income Black, Indigenous, and People of Color (BIPOC), may help address issues of mistrust in healthcare, potential low literacy, and other language barriers [8–12]; however, decision aids alone are unlikely to address navigating multi-step screening processes. Thus, decision aids can be more effective when combined with patient navigation [13]. Similarly, mailed FIT (for completion at home and return by mail) has been shown to be effective especially when combined with mailed or phone-based reminders and instructions [14]. However, despite evidence of the effectiveness of these strategies, implementation in settings such as rural FQHCs has been limited. Such multi-component interventions are often too cumbersome and resource intensive for FQHCs to implement due to the limited time and effort capacity of their personnel. Given the resource limitations and inconsistent patient engagement in FQHCs, mPATH^®^ (mobile Patient Technology for Health) CRC offers a scalable solution by automating patient outreach, providing accessible education, and overcoming literacy barriers. By delivering intervention components outside of regular appointments, mPATH^®^ CRC has the potential to mitigate many of the challenges faced by rural clinics and improve CRC screening rates among diverse, underserved populations.

mPATH^®^CRC was designed to “identify patients due for CRC screening, educate them on the commonly used screening tests, and help them select their best option, with the goal of increasing CRC screening rates” [15]. Thus far, mPATH^®^-CRC has been used in primary care clinics wherein patients use an iPad during check-in to view a decision aid about CRC screening options and answer questions about their screening preferences [15]. In a randomized controlled trial conducted in primary care practices affiliated with a large academic health system, an iPad version of mPATH^®^-CRC doubled the proportion of patients who completed CRC screening compared to usual care (30% versus 15%) [16]. However, while this study found mPATH^®^CRC to be effective as a clinical in-reach strategy (i.e., used for patients with appointments), less is known about factors effecting implementation and effectiveness of this type of technological solution with lower-resourced FQHCs that serve patients with relatively lower socioeconomic status. Particularly, delivery during appointments is challenging for FQHCs that have limited staff time and patients with less consistent appointment routines.

This study will implement mPATH^®^CRC with FQHCs using a novel outreach strategy that identifies patients and delivers intervention components to patients outside of regular appointments. This outreach strategy could increase reach and mitigate implementation barriers. The effectiveness will be evaluated using a pragmatic randomized controlled trial designed and anchored in the Process Redesign Framework for understanding both effectiveness and implementation in resource-constrained settings.

## Methods/Design

We will conduct a patient-level, pragmatic randomized controlled trial (RCT) to assess the impact of mPATH^®^-CRC on CRC screening rates over a three-year period. As a pragmatic trial, our goal is to determine if the intervention can improve current practice. Thus, the comparator arm patients will be assigned to usual care. Embedded within the RCT, we will use a convergent, mixed methods design for evaluation of the implementation process over the three-year implementation period. Implementation measures will also be used to understand unintended trial effects. All protocols have been reviewed and approved by the University of North Carolina at Chapel Hill and Wake Forest University institutional review boards, which granted a waiver of informed consent. Multiple data sharing, management, and security agreements were also reviewed and completed amongst UNC, FQHC, mPATH^®^-CRC, and other relevant partners. SPIRIT guidelines were used for reporting [17].

### Setting

Our study will be in rural southeastern North Carolina (NC) and work directly with an FQHC in the area. The FQHC operates eight health clinics in three rural counties, all of which use Epic for their EHR. These counties are the poorest in NC in both health and economic resources [18]. The FQHC is the main safety-net provider for the low-income population and serves between 12 and 15,000 patients a year, over 6,000 of whom are eligible for CRC screening. Nearly all of the FQHC’s patients are at or below 200% of federal poverty guidelines (97%), and half are on Medicaid or Medicare, one-fourth have private insurance, and one-fourth are uninsured [19]. Patients of this FQHC are racially and ethnically diverse, including American Indian (36%), African American (30%), and Hispanic/Latino (25%) patients [19]. In 2023, 72.5% of their patients were overdue for CRC screening [19].

### Participants

#### RCT participants

We will work with the participating FQHC to develop and validate a query of their EHR to identify patients aged 45 to 73 who are average risk for CRC, overdue for CRC screening, and have had at least one clinic visit in the past 12 months. We will exclude patients with a history of CRC or adenomas, total colectomy, family risk of CRC, or diagnosis of inflammatory bowel disease. Overdue for CRC screening is defined as no stool-based (FIT, FOBT) screening within the past one year, no stool DNA test within the past three years, and no colonoscopy within the past ten years.

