### RCT sampling and procedures

Figure 1 provides the study flow. A more detailed study schema is found in the Supplementary Materials. The FQHC will send an EHR query of all eligible (active) patients from their clinic sites approximately once per week to the research team (this list will be updated regularly to include newly added patients and remove previously selected patients or those who become current with screening). A biostatistician on our research team will use a computer-generated random sequence to select patients from the list within strata of appointment status and race/ethnicity: equal patients with an upcoming clinical appointment within approximately 21–45 days and patients without an upcoming clinical appointment (or an appointment greater than 45 days), and within each appointment status strata, equal patients from each of the four race/ethnicity groups represented in the FQHC’s patient population (White, Africa American, Hispanic, and American Indian). Next, we will randomize 1:1 to the mPATH^®^-CRC intervention and usual care within each appointment status and race stratum. We will repeat these sampling procedures until we reach our target sample of 1000 total patients after 8 months. We will follow this cohort for three total years, repeating the same outreach each year dependent on screening modality and completion (i.e., completion of colonoscopy in year 1 would no longer require follow-up, completion of FIT would require annual testing).

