#### Intervention arm

As shown in Fig. 1, patients selected for the intervention will be sent a text message that indicates they may qualify for a CRC screening and provides a link for further information, which directs them to the mPATH^®^-CRC interface. Patients without cell phone numbers will be mailed an invitation with the same information and a tiny URL and personal code to access the interface, although we anticipate this will be < 5% of participants. Within the mPATH^®^-CRC interface, patients will first answer a series of questions to confirm CRC screening eligibility and assess for risk factors that would change screening recommendations. If eligibility for routine CRC screening is confirmed, they will view a previously validated decision aid about CRC screening that provides information about their testing options, i.e., FIT or colonoscopy. After the video, patients are given the option to “self-order” either of those tests.

The FQHC will have its own secure mPATH^®^-CRC dashboard that displays patient requests for screening tests. The mPATH^®^-CRC system automatically emails designated staff a secure link to the dashboard when new patient screening requests occur. Notices of patients who select colonoscopy will be sent to the FQHC’s referral coordinators for further scheduling and communication. To integrate with the FQHC’s FIT processing and communication, patients who select FIT will be mailed a FIT kit using the FQHC’s usual FIT and lab vendors. Any patients who fail to engage with mPATH^®^-CRC interface within approximately 2 weeks of the initial text or mailed invitation will be mailed a FIT kit by default. The research team will have access to the mPATH^®^-CRC dashboards for implementation evaluation and will assist with prompting patient follow-up care and assistance, as appropriate.

All interface materials and communication will be offered in either English or Spanish, dependent on the patient’s language preference, including the decision aid video. Participants will also have the option to view a decision aid developed and culturally adapted in partnership with tribal communities in the state [20].

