### Measures

#### RCT primary outcomes

Since patients can decide between FIT or colonoscopy, the primary outcome will be CRC screening completion defined as meeting one of the following mutually exclusive pathways: (1) colonoscopy completion (regardless of indication), (2) at least one FIT test with normal FIT result, or (3) diagnostic colonoscopy following an abnormal FIT result. This measure is standard and comparable with prior CRC screening intervention studies [13, 21]. We will measure this outcome 6 months after randomization for all participants (including usual care). Outcomes will be based on encounter level data queried from the EHR, which mitigates issues of participant retention and provides pragmatic results.

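### Eligibility rests on test dates alone, so a patient with an earlier abnormal stool test and no later colonoscopy can be randomized, mailed a FIT by default and counted as screened on one normal result

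*Protocol article*

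**What the plan says.** All references are to the protocol article.

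- **RCT participants, overdue.** The definition has three look-back windows. The first covers FIT and FOBT: "Overdue for CRC screening is defined as no stool-based (FIT, FOBT) screening within the past one year". The other two windows are set in the same way, by time since the test: "no stool DNA test within the past three years, and no colonoscopy within the past ten years". None refers to a result.
- **RCT participants, exclusions.** "We will exclude patients with a history of CRC or adenomas, total colectomy, family risk of CRC, or diagnosis of inflammatory bowel disease". Patients must also be 45 to 73 years old, at average risk, and "have had at least one clinic visit in the past 12 months". Average risk is not defined further.
- **Intervention arm.** In the interface, "patients will first answer a series of questions to confirm CRC screening eligibility and assess for risk factors that would change screening recommendations". Those who have not engaged after about two weeks "will be mailed a FIT kit by default".
- **RCT sampling and procedures.** The cohort is followed for three years, "repeating the same outreach each year dependent on screening modality and completion".
- **RCT primary outcomes.** One of three routes to completion is "at least one FIT test with normal FIT result". Another is a diagnostic colonoscopy after an abnormal FIT.
- **RCT secondary outcomes.** A positive FIT earns coverage only once a colonoscopy is done. Prior screening is extracted from the EHR, but its stated use is for covariates or stratified analyses.

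**The concern.** A person with an abnormal stool test and no colonoscopy has an unfinished diagnostic question. Once the date window has passed, the overdue definition treats that person like someone who was never tested. The outreach can then send another screening FIT, in up to three yearly rounds, and a normal repeat result could falsely reassure both patient and clinic.

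Patient safety is what is mainly at stake. Second comes the meaning of the outcome: a normal repeat FIT in such a patient is scored as completed screening, although for an abnormal FIT found during the trial the plan asks for a colonoscopy.

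**Working it through.** The point involves no figure from the plan. The check is to run example patients through the stated rules. Each is assumed to meet the age and clinic-visit criteria and to have none of the listed exclusions.

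**1. Who passes the overdue definition?**

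| Example | FIT/FOBT window (1 y) | Stool DNA window (3 y) | Colonoscopy window (10 y) | Overdue? |
|---|---|---|---|---|
| A. Abnormal FIT 2 years ago, no colonoscopy | 2 > 1, clear | none | none | Yes |
| B. Abnormal stool DNA 4 years ago, no colonoscopy | none | 4 > 3, clear | none | Yes |
| C. Abnormal FIT 6 months ago, no colonoscopy | 0.5 < 1, blocked | none | none | No |
| D. Abnormal FIT 2 years ago, colonoscopy 18 months ago | 2 > 1, clear | none | 1.5 < 10, blocked | No |

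A and B are unresolved and pass. C is unresolved and is kept out only because the test is recent. D is resolved and is kept out by the colonoscopy window.

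The definition therefore removes resolved cases and keeps unresolved ones. Among enrolled patients, anyone with an abnormal FIT or FOBT 1 to 10 years ago, or an abnormal stool DNA test 3 to 10 years ago, has no later colonoscopy on record, because a colonoscopy in that span would have made them not overdue. For results more than ten years old this does not follow, since a colonoscopy could have come afterwards and still lie outside the window.

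**2. Does an exclusion stop A or B?** None of the listed conditions does. The average-risk criterion might, but the text does not link it to earlier stool-test results, so this cannot be settled from the article.

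**3. What happens after randomization to the intervention?** If A or B uses the interface, eligibility and risk questions come first; their content is not given. If A or B does not engage, those questions are never answered and a FIT is mailed. Informed consent is waived (Methods/Design), so no consent contact comes before the mailing. For this patient the EHR query is the only eligibility check that the article describes.

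**4. How is the result scored?** One normal FIT within six months of randomization meets the second route of the primary outcome. Nothing makes that depend on an earlier abnormal result.

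**5. How does the plan treat the same finding inside the trial?** After an abnormal FIT, completion or coverage requires a colonoscopy. Those rules do not say whether they reach results from before enrolment.

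**6. Effect on sample size.** If affected patients are excluded before randomization and replaced, the numbers stay at 500 per arm, and the inputs to the stated power are unchanged.

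**The case against.** The strongest reply is that this is a condensed article. It gives headline criteria for a query still to be developed and validated with the health center, and it refers to a more detailed schema in the Supplementary Materials. Handling of old abnormal results could sit there, or within average risk. That limits confidence, but it does not dispose of the point: the article states a definition and an exclusion list, and those rules, followed as written, admit the patient.

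Safeguards also exist:
- Every participant had a recent clinic visit, and half are sampled because an appointment is coming up in about 21–45 days.
- Interface users answer risk questions and may choose colonoscopy.
- The research team can see the dashboards and will help prompt follow-up where appropriate.
- Kits go through the clinic's usual FIT and laboratory vendors.
- Usual care also includes FOBT/FIT, so a repeat FIT in such a patient is not a risk found only in the intervention arm.
- Two institutional review boards approved the protocols.

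These make the exposed group smaller. None is tied to earlier abnormal results, and the interface questions miss exactly those who receive the default kit.

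A reader might infer that the plan contradicts itself. It does not do so literally: the in-trial colonoscopy rules define outcomes and are silent on results from before enrolment. The inconsistency is one of principle.

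**Conclusion.** The point holds as a patient-safety and eligibility gap of unknown size, with medium confidence. It rests on reading the stated criteria literally and on the absence of any text linking average risk, the query or the follow-up prompting to earlier stool-test results. The documents give no count or share of such patients.

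A reader might go further and infer a biased between-arm difference or a loss of power. The documents do not support that. Eligibility is the same in both arms, and a normal repeat FIT can count in either. Any figure for a shift would need an assumed share of affected patients. Multiplying that share by the difference in completion rates would describe keeping these patients and rescoring them as non-completers, which is not the remedy. If affected patients complete at their arm's rate and are replaced by others who do the same, the expected difference does not move.

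The change is still worth making, because the possible harm is avoidable and the remedy is nearly free.

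**What to change.** Add to the exclusions under RCT participants, and to the EHR query: *abnormal FIT, FOBT or stool DNA result with no later colonoscopy*. Apply it before randomization and identically for both arms, and return these patients to the clinic for diagnostic follow-up. State the colonoscopy condition explicitly, so that results older than ten years are handled correctly too. The primary outcome definition stays as it is. If the query already does this, saying so in the criteria settles the point.

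The cost is one condition in a query still to be built, one phrase in the text, and a slightly smaller pool. If the 72.5% overdue figure (Setting) applies to the roughly 6,000 patients eligible for screening, the pool is about 6,000 × 0.725 = 4,350 for 1000 places, before the clinic-visit and risk criteria. Equal sampling over 2 × 4 = 8 strata means 1000 / 8 = 125 places each. Pool sizes by stratum are not given, so replacement should be checked stratum by stratum.

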#### Implementation evaluation participants

We will invite all personnel in the FQHC’s clinics to participate, including primary care providers (physicians, physicians assistants, nurses), clinic staff (clerical and information systems/electronic health record management), and leadership. The only inclusion criteria are that they are employed by the participating clinical partner organization.

### RCT sampling and procedures

Figure 1 provides the study flow. A more detailed study schema is found in the Supplementary Materials. The FQHC will send an EHR query of all eligible (active) patients from their clinic sites approximately once per week to the research team (this list will be updated regularly to include newly added patients and remove previously selected patients or those who become current with screening). A biostatistician on our research team will use a computer-generated random sequence to select patients from the list within strata of appointment status and race/ethnicity: equal patients with an upcoming clinical appointment within approximately 21–45 days and patients without an upcoming clinical appointment (or an appointment greater than 45 days), and within each appointment status strata, equal patients from each of the four race/ethnicity groups represented in the FQHC’s patient population (White, Africa American, Hispanic, and American Indian). Next, we will randomize 1:1 to the mPATH^®^-CRC intervention and usual care within each appointment status and race stratum. We will repeat these sampling procedures until we reach our target sample of 1000 total patients after 8 months. We will follow this cohort for three total years, repeating the same outreach each year dependent on screening modality and completion (i.e., completion of colonoscopy in year 1 would no longer require follow-up, completion of FIT would require annual testing).

